### Outcomes

#### Patient-centred outcomes

The primary outcome measured is ADHD symptomatology measured using CGI, consisting of a 10-item total score and two sub-scores measuring restlessness/impulsivity (7 items) and emotional lability (3 items). The outcome is reported by carers (unblinded) and teachers (blinded), and each intervention is compared to usual care. Secondary outcomes are carer proxy health-related quality of life (CHU-9) and sleep. Resource use is collected by asking about medication use; further ADHD interventions being used; hospital, GP, social worker and police attendances; levels of absenteeism, exclusion and criminality; and teaching assistant and other help in school.

Resource use data is collected to enable an economic evaluation alongside a clinical trial. Evaluation will include health-related quality of life assessment, with utility measures based on the CHU-9D, the cost of consultations, medications, remedies, supplements and room hire, to enable QALY and ICER calculation. The time horizon is 1 year, during which time resource use will be collected from therapists, who complete therapist forms at each consultation documenting the time spent, the venue, medications or supplements given.

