#### Feasibility outcomes (Table 2)

Key feasibility criteria are the ability to recruit a cohort and to recruit to the interventions within the stated time frame of 2 years, by measuring recruitment rates and time taken. Numbers recruited in 2 years will be extrapolated to estimate the time needed to recruit to a full trial, and longer than 4 years will not be considered feasible. The feasibility of recruiting a representative cohort will document ADHD severity, number and type of co-morbidities, medications taken, resource usage, levels of exclusion, and criminality, and recruiting from nationally funded ADHD facilities such as special schools, secure units, NHS facilities and support services.

**Table 2 Tab2:** Feasibility criteria

Criteria	Measurement	Criteria for continuation to a full trial
Recruitment to cohort rates	Number recruited in 2 years	% recruited/sample size estimation. Minimum acceptable to proceed to a full-scale trial will consider the number of years needed to recruit the required sample size. Numbers recruited in 2 years will be extrapolated to determine how long a full trial would need to be. The required sample size will be divided by the percentage recruited in 2 years. Duration of the full trial of more than 4 years will not be considered feasible.
Recruitment to treatment rates	Percentage accepting offer	At least 30%. The percentage of participants refusing treatment will be considered to determine acceptable levels of refusal. Too many treatment refusers may lead to a high chance of a type II error and inadequate information to estimate critical parameters for a full trial with reasonable precision.
Treatment effects (statistical significance)	Standard mean difference (SMD) CGI	Mean = < .3. Since neither intervention has been tested in this form previously, estimation of the effect size cannot consider previous estimates. Since we need to know that therapies show some evidence of being helpful, a SMD of 0.3 in those implementing the therapies will be considered sufficient to proceed to full trial.
Treatment effects (clinical significance)	CGI *T* score	5 percentiles. A *T* score change of 5 percentiles is considered clinically significant, since the child has moved from one level of severity to another according to Conners (2009) [47].
Attrition: cohort	Number of PQs returned at 6 months	At least 30%
Attrition: consultations	Number of consultations attended	Adjustment of intervention provision

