Acceptability of TQ and CQ	Number of TQs and CQs completed at baseline and 6 months; number of email/telephone/ paper responses	Adjustment of measure, collection methods and trial parameters. Questions reworded or removed dependent on discussion with carers and teachers, and optimum means of delivering questionnaires explored
Adverse events	Clinicians records	No severe adverse events as defined by the Common Terminology Criteria for Adverse Events guidelines
Appropriate outcome measurement	Number of missing items	Adjustment of measure
Recruitment of therapists	Number recruited fulfilling criteria	At least two for each therapy
Statistical analysis	ANCOVA	Meets assumptions

Whether suitable homoeopaths and nutritional therapists can be recruited will be assessed, with recruitment of two therapists for each intervention considered the minimum required. The uptake of treatment will measure the number of appointments kept and missed; the taking of homoeopathic medicines; and the implementation of advice, diets, and the taking of supplements. At least 30% will need to have accessed treatment, and at least 70% of those to have attended at least three consultations, to continue to the full trial. It is anticipated that there may be high dropout rate and chaotic uptake. The percentage of participants refusing treatment will be considered to determine acceptable levels of refusal since too many refusers may lead to high chance of a type II error and inadequate information to estimate critical parameters for a full trial with reasonable precision.

Adverse events will be documented to measure the safety of the interventions using the Common Terminology Criteria for Adverse Events (CTCAE, 2010). Any severe adverse events as a result of treatment will mean the intervention will not continue to full trial.

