#### Statistical analysis

Statistical testing is exploratory since the study is not powered to detect statistical differences. It will be used to ensure that a difference can be seen from the interventions to proceed to the full trial, to inform sample size calculation, and to pilot test the statistical analyses selected. Analysis will focus on confidence interval estimation rather than hypothesis testing. IBM SPSS 21 statistical software [56] will be used. All statistical exploratory tests will be two-tailed with significance level (alpha) set to 5%, and 95% confidence intervals presented. Outcomes will be measured by parents and teachers at baseline, 6 months and 1 year. Both interventions tested will be compared with treatment as usual with parent and teacher measurements reported.

Missing data: post hoc tests will be performed to identify any differences between groups regarding whether data is missing completely at random or not at random. 6-month missing data will be imputed using Last Observation Carried Forward or mean substitution (for baseline data) according to tool developer recommendations [47].

‘Intention to Treat’ (ITT) analysis is used whereby participants offered treatment remain within the treatment group regardless of whether they take up the offer of treatment. The method used for statistical analysis of the outcome data will be regression analysis, with outcome change score as the dependent variable and group (homoeopathic treatment or nutritional therapy, analysed separately) as the independent variable. Analysis will control for the effects of gender, ADHD severity (CGI baseline score) and age.

The acceptability of the offer of treatment will be reported by presenting numbers for all patients offered treatment. Statistical tests will be carried out to identify characteristics of those who did and did not accept and receive treatment. Sub group analysis will explore the effect of treatment on those accessing that treatment, those taking/not taking ADHD medication and those with co-occurring autism.

The clinical effect of treatment will be explored by calculating standardised mean differences [57] for those offered and taking up the offer of each treatment to obtain sample size estimates.

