As a pragmatic trial, a disadvantage is that there is inevitable variation (noise), such as participants trying other interventions, changing medication dosage, or life events. All interventions are equally subject to such noise. A further potential disadvantage is that the offer of treatment, i.e., its acceptability, is measured, since ITT analysis is the primary analysis. The effectiveness of undertaking the treatment (per protocol analysis) is a secondary analysis. Measuring acceptability is an important issue in ADHD research where non-compliance is common. However, assessors may prioritise and require measurement of specific effects within treatments, such as effect due to therapist, supplement, dietary advice, homoeopathic medicine, etc. The real-life effectiveness of the two selected interventions has remained untested until now.

The TwiCs approach can be a cheap way to generate evidence regarding comparative effectiveness and potential to improve long term outcomes and can provide useful information to ADHD stakeholders including service providers. The current approach is inefficient, expensive, slow, difficult to compare, and not focused on improving outcomes for all those with ADHD in the longer term. If feasible, the STAR approach to testing interventions has the potential to contribute to the research canon and to patient outcomes.

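### Table 2's treatment-effect continuation rule has its inequality the wrong way round and is judged in children who took up treatment, although ITT of the offer is the primary analysis

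*Protocol article*

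**What the plan says.** All references are to the protocol article.

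- **Table 2, treatment effects (statistical significance).** The measure is "Standard mean difference (SMD) CGI". The continuation criterion opens with "Mean = < .3. Since neither intervention has been tested in this form previously". The same cell then gives its purpose, "Since we need to know that therapies show some evidence of being helpful", and its population, "a SMD of 0.3 in those implementing the therapies will be considered sufficient to proceed to full trial".
- **Statistical analysis.** ITT is defined by the offer, so children who decline stay in the arm they were offered. SMDs are to be calculated "for those offered and taking up the offer of each treatment to obtain sample size estimates". The results are to be presented with 95% confidence intervals.
- **Discussion.** The article accepts that the offer is what is measured, "since ITT analysis is the primary analysis", and calls the effect of undertaking treatment a secondary analysis.
- **Uptake.** The text after Table 2 sets the floor: "At least 30% will need to have accessed treatment". The Sample size section allows 20% for children who are ineligible or who decline.

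**The concern.** There are two faults in one decision rule.

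First, the printed inequality makes 0.3 a ceiling. Everything else in the cell makes it a minimum. No sign convention for the SMD is given. On the CGI a higher T score is worse (Table 1), so a benefit could be reported as a negative difference, and the reader cannot tell which form was meant.

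Second, the rule compares children who took up treatment with controls who were never offered it. Families who accept and persist select themselves, so randomisation does not protect that contrast. It also estimates a different quantity from the primary analysis. A trial of the offer dilutes the effect in takers by the proportion who decline, so 0.3 in takers does not mean that the ITT trial has 0.3 to detect.

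At stake are the decision to continue each intervention, the size of the full trial, and the 4-year duration limit in Table 2, which depends on that size.

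**Working it through.** **Inputs.** From the Sample size section: two groups, alpha 0.05, power 80%, planning SMD 0.4, about 100 per group, 40% attrition giving 166, and at least 30 per pilot arm. Two-sided testing is from Statistical analysis. The threshold of 0.3, the 30% uptake floor and the 4-year limit are from Feasibility outcomes. The cohort target of at least 140 is from Recruitment, and the 2-year time frame from Feasibility outcomes.

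**1. The plan's own figure.** n per group = 2 × (1.960 + 0.842)² / SMD² = 15.70 / SMD². At 0.4 this gives 15.70 / 0.16 = 98.1, so 99, against the stated 100. Then 100 / 0.6 = 166.7, against the stated 166. Both reproduce. The 0.3 threshold has no derivation to check.

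**2. Direction.** With 30 v 30, SE(SMD) ≈ √(1/30 + 1/30) = 0.258. Read literally, a rule of at most 0.3 would be met with probability Φ(0.3 / 0.258) = 88% when there is no effect, and Φ((0.3 − 0.4) / 0.258) = 35% when the true SMD is 0.4. As printed, the rule favours the ineffective treatment.

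**3. Uptake implied by the plan.** If ineligible and declining children together make up 20%, then at least 80% of those offered treatment accept. The figure is exactly 80% if all of the 20% are refusers, and higher if some are ineligible.

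**4. From takers to ITT.** Assume no effect in refusers, equal SDs and no selection bias. Then ITT SMD = uptake × takers' SMD.

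| Uptake | ITT SMD when takers' SMD is 0.3 | n per group (80% power) |
|---|---|---|
| 100% | 0.30 | 175 |
| 80% | 0.24 | 273 |
| 50% | 0.15 | 698 |
| 30% (floor) | 0.09 | 1,938 |

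**5. Power if the full trial is sized on the takers' 0.3.** With 175 per group, SE = √(2/175) = 0.107. At 80% uptake, power = Φ(0.24 / 0.107 − 1.96) ≈ 61%. At the floor, Φ(0.09 / 0.107 − 1.96) ≈ 13%.

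**6. Duration limit.** Three groups need 3 × 175 = 525 children on the takers' SMD and 3 × 273 = 819 on the ITT SMD at 80% uptake, both before attrition. The first understates the requirement by 294 children, and with it the projected duration.

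**7. Precision of the takers' contrast.** Chance of an observed SMD of 0.3 or more when there is no effect:
- 30 v 30 (SE 0.258): 12%
- 24 takers v 30, i.e. 80% uptake (SE 0.274): 14%
- 9 takers v 30, i.e. the floor (SE 0.380): 21%; the 95% CI around an observed 0.3 runs from about −0.44 to 1.04

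**8. Moving 0.3 unchanged to ITT.** This would require a takers' SMD of 0.3 / 0.8 = 0.375 at 80% uptake and 0.3 / 0.3 = 1.0 at the floor. With a true takers' SMD of 0.3 and 30 per arm, the chance of passing is 1 − Φ((0.3 − 0.24) / 0.258) = 41% at 80% uptake and 1 − Φ((0.3 − 0.09) / 0.258) = 21% at the floor. It is about 50% under the takers' rule.

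**The case against.** The operator is almost certainly a slip or a lost minus sign. The words beside it make the intent clear, and nobody would stop an effective treatment on the strength of it. That is fair as to intent, but the printed criterion still contradicts its own explanation and needs correcting.

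The ITT SMD of 0.09 is a corner case. The 30% is a floor, while the sample size section implies 80% or more, where the loss is from 0.30 to 0.24 and the false-go chance is close to that of the full arms. This stands. A reader might infer that the plan expects to proceed on a negligible ITT effect, but the document does not support that. The article does, however, anticipate erratic uptake, so values below 80% cannot be dismissed.

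Other criteria could still stop progression. At exactly 140 recruits in 2 years, 4 years yields about 280 children, fewer than either 525 or 819, so the duration limit would block both. Continuing is also subject to reviewers' comments and funding. This limits the harm. But 140 is a minimum, and with faster recruitment the choice of SMD could decide whether the limit is met. The article does not say which SMD drives the sample size.

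A reader might also infer that any one of four SMDs (carer or teacher, 6 months or 1 year) could satisfy the rule, with a correspondingly inflated false-go rate. The article nowhere says that any one suffices, and rater and time point are details that an article commonly leaves to the full protocol or SAP. That is not part of the error.

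**Conclusion.** The rule is wrong as written in two respects: the inequality contradicts the stated purpose, and the threshold applies to a self-selected group although ITT of the offer is primary. The realistic size of the second fault is an ITT SMD of about 0.24 where the rule suggests 0.30. That means 273 per group rather than 175, or about 61% power if the smaller number were used. The permitted extreme is 0.09 and about 1,940 per group.

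These figures assume no effect in refusers, equal SDs, no selection bias, and a full trial that keeps ITT as its primary analysis. Selection could move the takers' SMD either way. A reader might infer that it must flatter the treatment; the document gives no basis for the direction. The undersizing follows only if the takers' SMD is the one used, which the text leaves open.

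**What to change.** 1. Correct the operator and define the sign, so that the row reads as a minimum benefit on the CGI total.
2. Base go/no-go and the full-trial sample size on the randomised ITT SMD (offer v treatment as usual), reported with its 95% CI.
3. Set the ITT threshold from the expected uptake. If 0.3 in takers at 80% uptake is the intended target, the ITT threshold is about 0.24. If 0.3 is kept, state that the rule becomes materially harder to meet (step 8).
4. Keep the implementers' SMD as supportive only.

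Naming the rater and time point that count would be a useful clarification. A complier-average effect using the random offer as instrument is optional; at 30% uptake its SE would be about 0.258 / 0.3 = 0.86, so it would say little in a pilot of this size.

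The cost is one table row and a sentence or two in Statistical analysis. No new data are needed: the ITT comparison is already planned, and the SMD sentence, read as covering both groups, already includes those offered. One trade-off should be stated openly. With 30 per arm, a threshold of 0.24 is reached under no effect with probability 1 − Φ(0.24 / 0.258) ≈ 18%, against 12% at 0.3, so the confidence interval should be read alongside the point estimate.

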### Sample size

Sample size for the pilot trial is calculated to recruit at least 30 participants in each arm in order to estimate the pooled standard deviation of the outcome with a reasonable degree of precision for the full trial [48, 49]. We have estimated that attrition will be 20% based on a preliminary feasibility-controlled case series [50] and that a further 20% joining the STAR cohort will either not meet the first trial inclusion criteria or not accept the offer of treatment.

Sample size for the full trial will be based upon results obtained in the pilot. The calculation will be based upon the obtained effect size (SMD) for the primary outcome, significance (alpha error) of 0.05 and power of 80% and adjusted according to the levels of attrition observed. If an effect size of .4 is obtained in the pilot, then the outcomes of approximately 100 participants per group will be required. If estimated attrition of 40% is correct, then 166 participants per group will need to be recruited to the cohort.

Participants are recruited from registered charities, schools, word of mouth and support groups. The majority of participants are recruited from the city of Sheffield; however, participants are also recruited nationally and the feasibility of on-line treatments assessed.

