### Inclusion/exclusion criteria

Inclusion criteria for the STAR cohort are children aged 5–18 (inclusive) with a carer-reported diagnosis of ADHD (date, venue and diagnosing physician) and a carer-reported Conners Global Index (CGI) *T* score of at least 55 (denoting mild atypicality (Table 1). Inclusion criteria for the trial are a carer-reported CGI score of at least 65 (indicating a significant problem) (Table 1).

**Table 1 Tab1:** Interpretive guideline for Conners’ *T* scores and percentiles

*T* score	Percentile	Guideline
70+	98+	Markedly atypical (significant problem)
66–70	95–98	Moderately atypical (significant problem)
61–65	86–94	Mildly atypical (possible problem)
56–60	74–85	Slightly atypical (borderline)
< 30–55	< 2–73	Average (typical: should not raise concern)

Exclusion criteria to both cohort and trial are children below the age of 5 or adults over 18; children with terminal, severe, life-limiting conditions; and families where English is not written or spoken (as the project does not have funds to provide a translation service). Exclusion criteria to the trial are children currently receiving treatment by a homoeopath or a nutritional therapist and children with CGI *T* scores below 65.

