## Discussion

The results of this pilot trial will provide preliminary information on the feasibility of the TwiCs design to assess the effectiveness of interventions for children with ADHD to improve (long-term) outcomes. It will also provide preliminary information about the acceptability, clinical and cost-effectiveness of two potential interventions for ADHD. If feasibility criteria are met, then the study will continue to a full trial of these two interventions subject to reviewer’s comments and obtaining further funding.

Future plans are to develop the STAR cohort as a facility where interventions can be rigorously evaluated in a timely and efficient manner. This will entail expanding and ensuring the representativeness of the cohort and offering random samples of eligible participants a variety of mainstream and non-mainstream interventions. Recruitment of a representative cohort will focus on recruiting at-need populations such as teens, particularly those involved in criminality; hard to reach families; those with co-occurring autism; and those with multiple co-morbidities.

Advantages of the TwiCs design are the speedy recruitment of sufficient numbers. No deception is experienced by participants compared with placebo controlled trials. Trial conditions are similar to those patients could expect if consulting therapists in clinical practice and healthcare assessors might expect were they to commission treatments. All types of interventions, for example, complex, therapist-led and/or pharmaceutical treatments can be compared. Since the TwiCs design is designed to test multiple interventions, potential biases are equally distributed across groups.

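### Table 2 gives two CGI continuation thresholds that do not fit together: SMD 0.3 is called sufficient, and the next row adds 5 percentiles, a figure that does not match the severity levels in Table 1

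*Protocol article*

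**What the plan says.** Table 2 (Feasibility outcomes) has two rows labelled as treatment effects, one tagged statistical and one clinical significance. Both concern the Conners Global Index (CGI), and both have an entry in the column "Criteria for continuation to a full trial".

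- Statistical row: "a SMD of 0.3 in those implementing the therapies will be considered sufficient to proceed to full trial".
- Clinical row: the entry is 5 percentiles, with the explanation that a T "score change of 5 percentiles is considered clinically significant, since the child has moved from one level of severity to another".

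The severity levels come from Table 1 (Inclusion/exclusion criteria), which sets T-score bands beside percentile bands. Trial entry requires a carer-reported CGI T score of at least 65, and Randomisation stratifies at T 80.

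The Discussion says "If feasibility criteria are met, then the study will continue to a full trial", without saying whether every row must be met. Sample size gives a worked case that begins "If an effect size of .4 is obtained in the pilot" and leads to about 100 participants per group.

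**The concern.** A continuation rule should give one answer for one result. Here one row says that a given SMD is enough, and the next sets a further threshold for the same measure on another scale. If the first row is truly sufficient, the second has no force. If both must be met, the first is not sufficient.

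The second row cannot be applied as written. It mixes units (a T-score change counted in percentiles), it speaks of the child where the first row concerns a group effect, and it names no analysis group. The row that decides could therefore be chosen after the results are known.

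The choice also affects the next trial. By the plan's own sample-size method, the number per group is 175 at SMD 0.3 and 63 at SMD 0.5.

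**Working it through.** **1. The plan's own figure.** Inputs from Sample size: SMD 0.4, alpha 0.05 (two-sided, as Statistical analysis states for the pilot's tests), power 80%. n per group = 2 × ((1.960 + 0.842)/0.4)² = 98.1, so 99; the t-based value is 99.1, so 100. The plan says about 100. With 40% attrition, 100/0.6 = 166.7 against 166 stated. The figure reproduces, so the SMD there is an ordinary two-group difference. The same formula gives 175 at 0.3 and 63 at 0.5.

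**2. Width of a severity level in Table 1** (inclusive counts):

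| T band | Percentiles | Width in T points | Width in percentiles |
|---|---|---|---|
| 56–60 | 74–85 | 5 | 12 |
| 61–65 | 86–94 | 5 | 9 |
| 66–70 | 95–98 | 5 | 4 |
| 70+ | 98+ | open | open |

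No closed level is 5 percentiles wide; all are 5 T points wide. The stated reason therefore fits T points better than percentiles.

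**3. SD of the T score.** The protocol states none. Taking a norm mean of 50, Table 1 gives (60 − 50)/z(0.85) = 9.65, (65 − 50)/z(0.94) = 9.65 and (70 − 50)/z(0.98) = 9.74. A least-squares fit to all the T/percentile pairs gives SD 10.1 and mean 49.4. SD 10 is used below. It describes the norm population; the trial SD is unknown.

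**4. Second row as a between-group difference of 5 T points.** SMD = 5/SD:

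| SD | 7 | 8 | 10 | 12 | 12.5 | 16.7 |
|---|---|---|---|---|---|---|
| SMD | 0.71 | 0.63 | 0.50 | 0.42 | 0.40 | 0.30 |

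At SD 10, SMD 0.3 is 3 T points and 0.4 is 4. The two rows coincide only at SD 16.7, and a result of 0.4 clears both only at SD 12.5 or more. The planned analysis uses change scores. With equal SDs of 10 and baseline–follow-up correlation r, the SD of change is 10√(2(1 − r)): 11.8 at r = 0.3 (SMD 0.42), 10 at r = 0.5 (0.50), 7.7 at r = 0.7 (0.65).

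**5. Second row as literal percentiles** (normal curve, mean 50, SD 10). Fall in T points for a drop of 5 percentiles:

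| Start T | Fall | Fall/SD | End T |
|---|---|---|---|
| 65 | 3.1 | 0.31 | 61.9 |
| 66 | 3.5 | 0.35 | 62.5 |
| 68 | 4.3 | 0.43 | 63.7 |
| 70 | 5.4 | 0.54 | 64.6 |
| 75 | 9.1 | 0.91 | 65.9 |
| 80 | 13.7 | 1.37 | 66.3 |

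The hurdle depends on where the child starts, and from the entry score upward it is never below SMD 0.3.

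**6. Does either figure secure a change of level?** Not across the trial's range. Five percentiles from T 65 goes from the 94th to the 89th, inside the same level (86–94). It does cross a boundary from T 66 upward, but at T 80 that takes 13.7 T points. Five T points crosses a boundary in the closed levels, but 80 to 75 stays in the open top level.

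**7. Second row as a within-child or within-group change.** If the treated group improves by 5 points and usual care by m, SMD at SD 10 is (5 − m)/10: 0.5, 0.4, 0.3 and 0.2 for m = 0, 1, 2 and 3. The same 5-point change can thus sit above, at or below the first row. Children are selected at T 65 or more, so some fall is expected without treatment.

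**The case against.** The best defence is that the second row only defines a clinically meaningful change in a child. On that view it is not on the SMD scale and cannot conflict with the first row. Only the first row uses language about proceeding, and other cells in the column are actions (adjusting a measure or the provision of treatment), not pass marks. Position in the column is therefore weak evidence of a hurdle. This stands as a possible reading, but the article does not state it, and under it the row is an uncontrolled change.

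Other points also stand. The text says percentiles, so 5 T points is a conversion based on the row's stated reason. The SD is inferred from norms, and at 12.5 or above a result of 0.4 clears both rows. On the literal percentile reading, children near T 65 face a hurdle of about SMD 0.31, almost the same as the first row, and from T 66 upward a 5-percentile fall does cross a level boundary.

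A reader might infer that the full trial is planned on SMD 0.4 and could never be reached under the second row. The documents do not support that: 0.4 is a conditional worked example, and the real calculation is to use the effect that the pilot obtains. A reader might also compute the chance of passing each row with 30 per arm. That would not describe the stated criterion, which concerns those implementing therapy; uptake as low as 30% is acceptable, about 9 of 30.

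**Conclusion.** The point holds as a faulty decision threshold. Two CGI thresholds stand in one continuation column, one is called sufficient, no rule joins them, and the second has a figure that does not agree with Table 1 or secure the level change used to justify it.

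The size of the conflict is conditional. Read as a 5-T-point difference from usual care with SD about 10, the second row is SMD 0.5, and results from 0.3 up to 0.5, including the worked value of 0.4, pass one row and fail the other. The upper end moves to 0.42 at SD 12 and 0.71 at SD 7. Read as a within-child change, there need be no numerical conflict, but the criterion then lacks a comparison with usual care and regression to the mean could help meet it.

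It is not established that the rows must give opposite decisions. That needs T points, a between-group contrast, an SD low enough for the result in question, and a rule that both rows bind.

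**What to change.** Reword the two treatment-effect rows of Table 2:

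1. Name one deciding effect criterion, as an estimated difference from treatment as usual in CGI T points, with its SMD equivalent and the SD used for the conversion.
2. State the analysis group, either all those offered treatment or those implementing it.
3. Correct the 5-percentile figure so that it agrees with Table 1. If a change of level is kept as the reason, say how it applies to children in the open 70+ level.
4. State that the other row is descriptive and does not decide. Alternatively, delete *sufficient* and state that both rows must be met.

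The worked example under Sample size can stay. The cost is the wording of two table rows, and a commitment to one hurdle before results are seen; that hurdle may look less favourable than SMD 0.3. No data collection changes.

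### Table 2's clinical-significance criterion is measured on the CGI T score but set at 5 percentiles, so the T change it demands varies about fourfold with baseline severity; two eligibility descriptions also disagree with Table 1

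*Protocol article*

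**What the plan says.** All references are to the protocol article.

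- **Feasibility outcomes, Table 2**, row on treatment effects (clinical significance): the measurement is the CGI T score and the criterion is 5 percentiles. The reason given is that a T "score change of 5 percentiles is considered clinically significant, since the child has moved from one level of severity to another".
- **Inclusion/exclusion criteria, Table 1** defines the levels on both scales:
  - T 70+, percentile 98+: "Markedly atypical (significant problem"
  - T 66–70, percentile 95–98: "Moderately atypical (significant problem"
  - T 61–65, percentile 86–94: "Mildly atypical (possible problem"
  - T 56–60, percentile 74–85: "Slightly atypical (borderline"
  - T 55 and below, percentile 73 and below: "Average (typical: should not raise concern"
- **Inclusion/exclusion criteria, text**: the cohort requires a T "score of at least 55 (denoting mild atypicality (Table 1", and the trial requires "a carer-reported CGI score of at least 65 (indicating a significant problem".
- **Randomisation**: severity is stratified at a T score of 80 or more against under 80.
- **Table 2**, adjacent row: an SMD of 0.3 on the CGI is treated as enough to go on to the full trial.

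**The concern.** A T score is linear in standard deviations and a percentile is not. In the upper tail, where every child in this trial lies, one percentile covers more and more T points as severity rises. A threshold fixed in percentiles therefore asks for a different symptom change at each baseline score. The stated reason, a move between severity levels, points to Table 1, where the closed levels share a common width in T points and not in percentiles.

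At stake is a pre-specified criterion for continuing to a full trial. An assessor who takes the word percentiles literally and one who takes it to mean points can reach different decisions from the same data. The eligibility descriptions are a smaller matter: they cite Table 1 for labels that Table 1 does not give.

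**Working it through.** **1. Level widths, from Table 1.**

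| Level (T) | T scores covered | Percentiles | Percentile width |
|---|---|---|---|
| 56–60 | 5 | 74–85 | 85 − 74 = 11 |
| 61–65 | 5 | 86–94 | 94 − 86 = 8 |
| 66–70 | 5 | 95–98 | 98 − 95 = 3 |
| 70+ | open | 98+ | at most 2 |

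The figure 5 is the common width in T points. It is not the percentile width of any level.

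**2. Conversion (assumption: normal T scale, mean 50, SD 10).** Percentile P(T) = 100 × Φ((T − 50)/10). Against Table 1: T 61 gives 86.4 (table 86), T 65 gives 93.3 (94), T 66 gives 94.5 (95), T 70 gives 97.7 (98). Agreement is within about 1 percentile over T 61–70. It is poorer at T 55 (69.1 against 73), but no fall of 5 percentiles from an eligible trial score ends that low.

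**3. T points needed for a 5-percentile fall.** D(T) = T − [50 + 10 × Φ⁻¹(P(T)/100 − 0.05)]. The last column gives the reverse, P(T) − P(T − 5).

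| Baseline T | P(T) | P(T) − 5 | T reached | T points needed | Percentiles in a 5-point fall |
|---|---|---|---|---|---|
| 65 | 93.32 | 88.32 | 61.91 | 3.1 | 9.2 |
| 66 | 94.52 | 89.52 | 62.55 | 3.5 | 8.1 |
| 70 | 97.72 | 92.72 | 64.56 | 5.4 | 4.4 |
| 75 | 99.38 | 94.38 | 65.87 | 9.1 | 1.7 |
| 80 | 99.87 | 94.87 | 66.32 | 13.7 | 0.5 |
| 85 | 99.98 | 94.98 | 66.43 | 18.6 | 0.1 |

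The need is 4.9 points at T 69 and 5.4 at T 70, so the two readings cross between those scores. From 65 to 80 the demand rises by a factor of 13.7/3.1 = 4.4.

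**4. Check without the normal assumption.** Linear interpolation of the Table 1 points gives 2.5 T points from 65, 3.0 from 66 and 5.5 from 70. A score of 80 lies between percentiles 98 and 100, so a 5-percentile fall ends between percentiles 93 and 95, which is T 64.5 to 66: a fall of 14 to 15.5 points. The range is the same.

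**5. Opposite answers on the same data.** A fall from 65 to 61 is 4 T points and 94 − 86 = 8 percentiles in Table 1: it meets the percentile reading and misses 5 T points. A fall from 80 to 75 is 5 T points and 0.5 percentile: the reverse.

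**6. Does the written rule change the level?** From T 65 it ends at 61.9, still within 61–65, so it is met with no change of level. From every whole score of 66 or more it ends in a lower level.

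**7. Against the SMD row.** With an assumed SD of 10, 5 T points is 5/10 = 0.5 and an SMD of 0.3 is 3 T points. For an SD of 8 to 12, 5 T points is 0.63 to 0.42.

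**8. Eligibility descriptions.** The text calls T 55 mild atypicality; Table 1 puts 55 in its average level and begins the mild level at 61. The text calls T 65 a significant problem; Table 1 puts 65 among possible problems and begins significant problems at 66.

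**The case against.** The strongest reply is that the rule, read literally, largely does what its rationale says. Table 2 asks only for a move between levels, and a 5-percentile fall achieves one from every whole score of 66 upward. Among eligible trial scores, only exactly 65 fails. That stands, and a reader who infers from the level widths that the rule generally fails to move a child between levels would be wrong.

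Three further points also stand:

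- The failure in the open top level (80 to 75 remains in 70+) belongs to a 5-T-point rule, not to the written one.
- A reader might infer that the criterion is nearly out of reach in the 80+ stratum. The documents give neither an expected T change nor its SD, so that cannot be said.
- The decision weight is limited. This is one of 11 rows in Table 2, the testing is exploratory, and the full-trial sample size is based on the SMD.

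If the row is applied to a group mean, there is a single threshold and not a spread across children. This narrows the point but does not remove it: the T change required then depends on the mean baseline in the same way, and Table 2 does not say which use is meant.

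On eligibility, inclusion at 65 or more and exclusion below 65 agree. The cut-offs are workable; only their descriptions are at fault.

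**Conclusion.** The criterion mixes two scales and should be restated. The T change it requires runs from about 3 points at the entry score of 65 to about 14 at 80, and more above that. Up to T 70 this can be read from Table 1 alone; above 70 it rests on the assumed normal scale, or on the bound that the percentile lies between 98 and 100. Both routes give the same picture.

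It is tempting to say that 5 T points was meant and that the unit is simply wrong. The level widths and the rationale make that likely, but the text does not say so, and the sponsor should confirm it. What the document establishes is a threshold whose unit does not suit its measure and whose level of application is open.

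The label mismatch is real but secondary: for the trial it touches only children scoring exactly 65, and the T 55 description concerns the cohort alone. Taken together, this is a should-fix point.

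**What to change.** 1. State the threshold in T-score points. Five points matches the Table 1 level width; the sponsor should confirm that this was the intention.
2. Say whether it applies to each child's change or to a group mean. Recasting it as an intention-to-treat difference between groups would be a new estimand, so that should be a deliberate choice and not a by-product of correcting the unit.
3. Check it against the 0.3 SMD row. Five T points is an SMD of 0.5 at an SD of 10, so the two rows would set different bars; say how they combine.
4. If 5 T points is adopted, do not justify it by a change of level for scores above 75, where a 5-point fall stays in the open 70+ level.
5. Reconcile the descriptions of T 55 and T 65 with Table 1, most simply by correcting the descriptions and leaving eligibility unchanged. Assign T 70 to one row, since it now appears in two.

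These are wording changes with no data cost, to be made before the continuation decision. Moving the cut-offs to match the labels would be different in kind, because it changes who is eligible.
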